Within each intervention municipal area, a local Community Advisory Board (CAB) is created of key stakeholders, including representatives of local and regional government, directors of PHC services, non-governmental organisations active in providing counselling and treatment services for alcohol and mental health, academic experts and local media. The CABs meet regularly during the course of the study, giving advice on tailoring materials for local use, giving advice on adoption mechanisms, support systems and communication campaigns to support the action and preparing for sustainability and scale-up at the end of the action.

The units of allocation and analysis, that is, study participants, are 54 PHCUs and the providers working in them. Within each PHCU, eligible providers include any fully trained healthcare provider working in the PHCU and involved in medical and/or preventive care. Within each PHCU, individual providers decide themselves whether or not to participate in the study; those who do sign an informed consent for their participation. Based on the five-country ODHIN study, we estimate that approximately two-fifths of providers will consent to join the study.^61^ The overall study design is summarised in figure 1. Fifty-four PHCU are invited to join the study until 27 are achieved within each of the two municipal areas (intervention and control) across the three countries (nine per municipal area within each of the three countries).

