**Figure 1 F1:**
[figure not shown]
Study flow diagram.

Within each intervention municipal area, a user panel (UP) is created of providers and patients drawn from the PHC centres to advise on the tailoring of patient and provider materials and on provider training programmes.

For the first 6 months of the 18-month implementation and test period, a four-arm design is adopted, figure 2. Within the comparator municipal area, 12 PHCUs out of the 27 are randomly allocated to control (Arm 1), and 15 are allocated to receive short training to implement a short clinical package (Arm 2). Within the intervention municipal area, in which all 27 PHCU receive municipal action, 15 PHCUs are randomly allocated to receive short training to implement a short clinical package (Arm 3), and 12 PHCUs are allocated to receive standard training to implement a standard clinical package (Arm 4). Random allocation was undertaken using Excel random number generator.

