### Statistical tests of key hypotheses

#### Primary study goal

Multilevel regression analyses will be undertaken at 12 months’ time of the implementation test period, using cumulative results at months 1 to 12, and at 18 months’ time using cumulative results months 1 to 18. Both analyses will include covariates of country and results during baseline month, analysed at the levels of the PHCU by study arm, taking into consideration the hierarchical nature of the data. For any PHCU that drops out during the study, outcome values for subsequent measurement points will be set at the last value obtained.

##### Hypothesis 1

Municipal action leads to more sustainable coverage among PHCU that receive training. We will compare results on primary outcome after 18 months with results after 12 months between Arm 3 versus Arm 2 via regression.

Dependent variables:

For each PHCU, cumulative results of months 1–18 of number of patients whose alcohol consumption is measured with AUDIT-C per 1000 registered patients; and cumulative results of months 1–12 per 1000 registered patients.

Random effects:

Country as random intercept (test for inclusion).

Independent variables:

Proportion of consulting patients who have their alcohol consumption measured with a completed AUDIT-C instrument during the baseline measurement month.Condition:Municipal action (yes vs no).Covariate:Proportion of consulting patients who have their alcohol consumption measured with a completed AUDIT-C instrument during the baseline measurement month.

It is postulated that coverage for Arm 3 will be significantly higher than for Arm 2.

##### Hypothesis 2

Training leads to higher coverage than no training. For both months 1–12 and months 1–18, compare cumulative coverage as per primary outcome between Arms 1 and 2 via multilevel regression analyses.

Dependent variable

Cumulative results months 1–12, and cumulative results months 1–18 of number of patients whose alcohol consumption is measured with AUDIT-C per 1000 registered patients withPHCU.

Random effects:

Country as random intercept (test for inclusion).

Independent variables:

Condition:Training (Arm 2 vs Arm 1).Covariate:Proportion of consulting patients who have their alcohol consumption measured with a completed AUDIT-C instrument during the baseline measurement month.

It is postulated that coverage for Arm 2 will be significantly higher than for Arm 1.

##### Hypotheses 3

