### Sample size calculations for main hypothesis

As the outcome of the primary study goal is predicted to be Arm 3>Arm 2>Arm 1, we compared both Arm 2>Arm 1, and Arm 3>Arm 2.

Our power calculations are based on the following assumptions: given an average size of a PHCU of approximately 15 000 adults, with an average of 1500 new consultations per month, we expect a cumulative coverage after 12 months of 0.0325 of the registered adult population to have had their alcohol consumption measured in the control condition (Arm 1) (data extrapolated from month 3 and month 9 assessments of control group from ODHIN study;^22 24^ [name], personal communication). For the short clinical package and short training (Arm 2), we expect this to increase to 0.075 (data extrapolated from month 3 and month 9 assessments of training group from ODHIN study;^22 24^ [name], personal communication). Although the WHO Phase IV study predicts an additional beneficial impact of municipal support,^41^ precise empirical data is not available—however, we consider an estimate for Arm 3, with municipal support, to be 0.15, a proportion that would need to be achieved to consider municipal support to be worthwhile. To detect the difference between Arm 2 and Arm 1, assuming a design effect of 15 PHCUs (clusters) across the three municipal areas in Arm 2, with 15 000 patients (items), and 12 PHCUs (clusters) in Arm 1, with 15 000 patients (items), with an ICC for PHCUs of 0.03 (data from ODHIN study;^22 24^ [name], personal communication) we would have 82% power at a significance level of 5%.^87^ For the difference between Arm 3 and Arm 2 (15 PHCUs/clusters in each arm), we would have 96.5% power.

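### Country is an unconditional covariate in the general analysis statement but, in each hypothesis model, only a random intercept subject to an inclusion test on three levels; the model should be fixed in advance, although the numerical harm is small

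*Protocol article*

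**What the plan says.** The opening paragraph under Primary study goal (Statistical tests of key hypotheses) describes two analyses. It says "Multilevel regression analyses will be undertaken at 12 months’ time of the implementation test period", adds a second at 18 months, and continues: "Both analyses will include covariates of country and results during baseline month". No condition is attached.

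The itemised models for Hypotheses 1 and 2 follow. Under random effects, each gives "Country as random intercept (test for inclusion". Country does not appear among their independent variables or covariates. Hypothesis 3, analysed at month 6, has the same random-effects line. No test, threshold or between-country variance is given.

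Country is part of the design. Methods and analysis recruits PHCUs as "nine per municipal area within each of the three countries", and control areas are chosen in the same cities as the intervention areas.

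**The concern.** The same section fixes country twice, and the two statements cannot both be followed. One makes country a certain covariate; the other makes it a random effect that has to pass a test. Two analysts working from this text could fit different primary models.

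The test is also a poor rule for this factor. A variance estimated from three countries has 2 degrees of freedom, so a non-significant result says little about whether country matters. Hypothesis 1 has two dependent variables, coverage over months 1–12 and over months 1–18. If the test is run for each, country could be kept at one time point and dropped at the other within a single comparison. Hypothesis 3 decides whether Arms 3 and 4 are merged, so its model should also be settled before the data are seen.

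**Working it through.** **1. The stated power.** Inputs from Sample size calculations: Arm 1 coverage 0.0325 ("we expect a cumulative coverage after 12 months of 0.0325 of the registered adult population"), Arm 2 coverage 0.075 ("we expect this to increase to 0.075"), Arm 3 coverage 0.15, 15 000 adults per PHCU, ICC 0.03, and 12, 15 and 15 PHCUs.

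- Design effect = 1 + 14 999 × 0.03 = 450.97. Effective n = 12 × 15 000 / 450.97 = 399.1, and 15 × 15 000 / 450.97 = 498.9.
- Arm 2 v Arm 1: SE = √(0.0325 × 0.9675/399.1 + 0.075 × 0.925/498.9) = 0.01476. Then 0.0425/0.01476 = 2.88, and power = Φ(2.88 − 1.96) = 82.1%.
- Arm 3 v Arm 2: SE = √((0.075 × 0.925 + 0.15 × 0.85)/498.9) = 0.01987. Then 0.075/0.01987 = 3.78, and power = Φ(3.78 − 1.96) = 96.5%.

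Both stated figures reproduce with a two-sided 5% test. Neither calculation has a country term, so the treatment of country does not affect them.

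**2. How often the test would drop country.** Layout for Hypothesis 2: 27 PHCUs, nine per country, 12 in Arm 1 and 15 in Arm 2. Let s be the share of PHCU-level variance due to country. The article gives no value, so s is varied. Assumptions: a 5% test and a roughly normal PHCU-level outcome.

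An exact F-test can be checked by hand. After three country means, arm and the baseline covariate, 27 − 5 = 22 degrees of freedom remain, and the critical value is F(2, 22) = 3.443. Put x = 3.443 / (1 + 9s/(1 − s)). Then P(kept) = (1 + 2x/22)^(−11).

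- s = 0.10: x = 3.443/2 = 1.722, kept 20%, dropped 80%.
- s = 0.20: x = 3.443/3.25 = 1.059, kept 36%, dropped 64%.
- s = 0.30: x = 3.443/4.857 = 0.709, kept 50%, dropped 50%.
- s = 0.50: x = 3.443/10 = 0.344, kept 71%, dropped 29%.

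For a random intercept a REML likelihood-ratio test is the more likely choice. Simulated drop rates (100 000 draws each):

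| Country share s | Cut-off 2.71 (halved p) | Cut-off 3.84 |
|---|---|---|
| 0.10 | 85% | 90% |
| 0.20 | 70% | 77% |
| 0.30 | 55% | 63% |
| 0.50 | 33% | 40% |

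The variance estimate is exactly zero in about 62% of samples when country has no effect, and still in about 39% at s = 0.10. Across all tests tried (F, REML and ML), country is dropped more often than kept only while s is below about 0.25 to 0.45.

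**3. What the rule does to the arm comparison.** Arms are assumed balanced within country (4 v 5 PHCUs per country for Hypothesis 2). The noncentrality is 2.88 from step 1, total variance is held fixed, and the baseline covariate is left out. Power for Hypothesis 2 (40 000 draws):

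| s | Always fixed | Tested, cut-off 2.71 | Tested, cut-off 3.84 | Never included |
|---|---|---|---|---|
| 0.10 | 82.7% | 82.3% | 81.9% | 81% |
| 0.20 | 86.7% | 86.1% | 85.7% | 83% |
| 0.30 | 91.1% | 90.6% | 90.1% | 85% |

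The tested rule loses 0.4 to 1.0 points here; repeat simulations gave 0.3 to 1.1. Its type I error was 4.3% to 5.2% for s from 0 to 0.5. A separate simulation with an F-test as the rule gave 4.4% to 5.4%, and power of 79.7% against 80.1% for always including country at s = 0.20. For the Hypothesis 1 layout (5 v 5 per country, inferred from 15 v 15) the same comparison gave 94.9% against 95.0%.

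Under this balance, and before the baseline covariate, the arm estimate is numerically the same with and without country. Only its standard error changes.

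**4. Cost of always including country when it explains nothing.** Noncentral t with noncentrality 2.88: 79.04% on 25 degrees of freedom and 78.76% on 23, a loss of 0.28 points.

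**The case against.** The strongest reply is that this is a wording slip with almost no effect. The test drops country mainly when the observed country differences are small, which is when dropping it costs little, and step 3 bears this out. The drop rates rest on an assumed country share. The three cities are in different countries, so a share of 50% or more cannot be excluded, and country would then usually be kept. The baseline covariate, present in every model, may absorb part of any country difference. The choice of test and threshold can reasonably be left to a fuller document. Fixed versus random with three levels is partly a matter of preference, and a random intercept could loosely be called a covariate.

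Most of this stands, and it limits the size of the point. It does not remove the contradiction: even on the loose reading of covariate, one sentence promises inclusion and the models make it conditional.

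A reader might infer more than the article supports:

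- That the nominal p-value is invalidated. The simulated type I error stays close to 5%.
- That Hypothesis 1 stops being a within-city comparison. With balanced arms the estimate does not change, and confounding between areas is addressed separately by choosing control areas in the same cities and by propensity score matching.
- That power falls from 83–91% to 79%. That sets fixed inclusion against a calculation with no country term, which is not the protocol's rule. Even never including country gives 81% to 85% in step 3.
- That the general sentence contradicts all three models. It covers months 12 and 18 only, so the month-6 Hypothesis 3 model shares the weak rule but not the contradiction.

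**Conclusion.** The point holds as a specification fault. For months 12 and 18 the article promises country as a covariate and then makes it conditional in the Hypothesis 1 and 2 models. The inclusion test has little power on three levels: a REML likelihood-ratio test would drop country in about 55% to 90% of trials at assumed shares of 10% to 30%, and in about 33% to 40% at 50%. Whether country would usually be dropped cannot be settled from the article.

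The consequence is a primary model left open until the data are seen. In power it is worth about 0.3 to 1 point, with type I error close to 5%. These figures assume arms balanced within country. The article gives nine PHCUs per area per country but not the split of arms within each country. If the split is uneven, dropping country would also move the arm estimate, which is a further reason to settle its role in advance.

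**What to change.** In the models for Hypotheses 1, 2 and 3, replace the conditional random intercept with country as a fixed effect (three levels), always included, and delete the inclusion test. This agrees with the opening paragraph of the section on country. Country is the only random effect listed in these PHCU-level models, so the description of them as multilevel needs adjusting at the same time, in that paragraph and under Hypothesis 2.

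The cost is a few words of text and two degrees of freedom: about 0.3 power points if country explains nothing. The sample size and the stated power do not change.

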#### During 1-month baseline measurement period for Arms 1–4

##### Provider-based measurement and assessment of alcohol consumption and comorbid depression and record of advice and treatment given (tally sheets)

Based on the validated methodology of the ODHIN project,^22 24^ PHC providers will be asked to document activity by completing anonymous paper tally sheets that record eligible patients’ (aged 18+ years) AUDIT-C scores,^65^ and, if administered (as documented in online supplementary file S1, online supplementary table S1), AUDIT-10,^66^ Patient Health Questionnaire (mental disorders), 2-item version (PHQ-2)^67^ and PHQ-9^68^ scores, and the advice or treatment given to each patient. The tally sheets will record the age, sex and educational level of the patient, the latter as a proxy measure of socioeconomic status. PHCUs will return data on the number of adult (aged 18+ years) consultations per provider for the 1-month baseline measurement period. Tally sheets will be delivered to the PHCU to be distributed to the participating providers at the beginning of the 1-month baseline measurement period and collected at the end of the period, with no other contact during the period.

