### Outcomes

#### Primary outcome

The primary outcome will be the cumulative proportion of the number of adults (aged 18+ years) registered with the PHCU that have their alcohol consumption measured with a completed AUDIT-C instrument during the study period (coverage). The number of adults registered is provided by the administrative office of the PHCU and includes all adult patients covered by the PHCU, whether or not they consult during the 18-month implementation test period.

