#### Secondary outcomes

Proportion of consulting patients who have their alcohol consumption measured by AUDIT-C: calculated as the number of adults who have their alcohol consumption measured by AUDIT-C divided by the total number of adults who consult the PHCU during the same time period per participating provider and per PHCU.At risk population receiving advice and/or treatment for heavy drinking: calculated as the number of adults with an AUDIT-C score of 8+ who receive brief advice and/or referral for their heavy drinking divided by the total number of patients with an AUDIT-C score of 8+ per participating provider and per PHCU. Information will also be collected on the number of patients with an AUDIT-C score of <8 who receive brief advice and/or treatment for their heavy drinking.Proportion of patients with AUDIT-C score of 8+ who receive assessment for depression: calculated as the number of consulting adults with an AUDIT-C score of 8+ who complete PHQ-2 divided by the total number of patients with an AUDIT-C score of 8+ per participating provider and per PHCU.At risk population receiving advice and/or treatment for comorbid depression: calculated as the number of adults with a PHQ-2 score of 3+ who receive a patient leaflet and/or referral for their depression divided by the total number of patients with a PHQ-2 score of 3+ per participating provider and per PHCU.Provider attitudes: attitudes of the participating providers will be measured by the SAAPPQ.^65^ The responses will be summed within the two scales of role security and therapeutic commitment. Individual missing values for any of the items in a domain will be assigned the mean value of the remaining items of the domain before summation.

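### The baseline covariate is per consulting patient while the outcome is per registered adult, so the Hypothesis 1 model does not adjust for differences in consultation volume between non-randomised areas

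*Protocol article*

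**What the plan says.** Under Primary outcome, the denominator of coverage "includes all adult patients covered by the PHCU, whether or not they consult during the 18-month implementation test period". The models under Statistical tests of key hypotheses use the same scale: the dependent variable is the cumulative "number of patients whose alcohol consumption is measured with AUDIT-C per 1000 registered patients".

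The general statement under Primary study goal says that "Both analyses will include covariates of country and results during baseline month". Each hypothesis then settles what the baseline result is. For Hypotheses 1, 2 and 3 it is the "Proportion of consulting patients who have their alcohol consumption measured with a completed AUDIT-C instrument during the baseline measurement month", and for Hypothesis 1 it is listed twice. Country enters as a random intercept, subject to a test for inclusion. No other baseline measurement appears in any of the three models.

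Under Secondary outcomes, the consulting proportion is defined as adults measured "divided by the total number of adults who consult the PHCU during the same time period per participating provider and per PHCU". The ingredients for a covariate on the outcome's scale are collected. At baseline "PHCUs will return data on the number of adult (aged 18+ years) consultations per provider for the 1-month baseline measurement period", and registered adults are obtained from every contacted PHCU (PHCU and provider level information).

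Allocation differs by contrast. Arms 1 and 2, and Arms 3 and 4, are randomised within their area. The municipal areas that separate Arm 3 from Arm 2 were chosen by the investigators. For that comparison the protocol promises propensity score matching on municipal and PHCU data.

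**The concern.** Coverage per registered adult is the product of two factors: the share of consultations at which alcohol is measured, and the number of consultations per registered adult. The covariate reflects the first factor only. Two PHCUs with the same covariate value can therefore start from different coverage on the scale being analysed.

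This matters most for Hypothesis 1. If registered adults in the intervention areas attend more often than those in the control areas, Arm 3 will show higher coverage with no effect of municipal action, and the model has no term to absorb the difference. A difference the other way would hide a real effect. Because the outcome is cumulative, a constant difference in volume also widens the gap between months 12 and 18, which is the pattern Hypothesis 1 takes as evidence of sustained benefit.

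**Working it through.** **Inputs from the protocol (Sample size calculations for main hypothesis).** Average PHCU of 15 000 adults and 1500 consultations a month. Expected 12-month coverage of 0.0325 (Arm 1), 0.075 (Arm 2) and 0.15 (Arm 3). Intracluster correlation 0.03. Stated power 82% (Arm 2 versus Arm 1; 15 and 12 PHCUs) and 96.5% (Arm 3 versus Arm 2; 15 each).

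**The plan's own figures.** Design effect = 1 + (15 000 − 1) × 0.03 = 450.97. Effective sample sizes are 12 × 15 000 / 450.97 = 399.1 and 15 × 15 000 / 450.97 = 498.9. With a two-sided 5% normal test and unpooled variance:

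- Arm 2 v Arm 1: SE = √(0.0325 × 0.9675 / 399.1 + 0.075 × 0.925 / 498.9) = 0.01476. z = 0.0425 / 0.01476 − 1.96 = 0.92, power 82.1%.
- Arm 3 v Arm 2: SE = √(0.075 × 0.925 / 498.9 + 0.15 × 0.85 / 498.9) = 0.01987. z = 0.075 / 0.01987 − 1.96 = 1.82, power 96.5%.

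Both stated powers reproduce. They use no covariate, so this point does not touch them.

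**Decomposition.** Coverage after T months = (share of consultations measured) × (consultations per registered adult per month) × T, counting each measured consultation as one adult measured. The monthly rate is 1500 / 15 000 = 0.10, or 1.2 over 12 months. The planned coverages then correspond to measuring 0.0325 / 1.2 = 2.7%, 0.075 / 1.2 = 6.25% and 0.15 / 1.2 = 12.5% of consultations.

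**Effect of a volume difference alone.** Let both arms measure 6.25% of consultations throughout, and let Arm 3 areas have r times the consultation rate. The gap is 0.075 × (r − 1) at 12 months. At 18 months the common level is 0.0625 × 0.10 × 18 = 0.1125, so the gap is 0.1125 × (r − 1). The planned Arm 3 minus Arm 2 effect is 0.15 − 0.075 = 0.075. The protocol gives no spread for consultation rates, so the values of r are assumptions.

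| r | Arm 3 coverage, 12 months | Gap, 12 months | Gap, 18 months | 12-month gap as share of planned effect |
|---|---|---|---|---|
| 1.1 | 0.0825 | 0.0075 | 0.011 | 10% |
| 1.25 | 0.094 | 0.019 | 0.028 | 25% |
| 1.5 | 0.1125 | 0.0375 | 0.056 | 50% |
| 2 | 0.15 | 0.075 | 0.1125 | 100% |

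The listed covariate takes the same value in both arms in every row.

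**Illustrative simulation.** No true effect, 15 v 15 PHCUs, with assumed between-PHCU spreads. The size of these results depends on those assumptions; only their direction should be relied on.

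- r = 1.25: the listed covariate left about +18 per 1000, with 18–24% rejection at nominal 5%. Baseline coverage per registered adult left about +2 per 1000 and 5–6%. The listed proportion plus baseline consultation rate and participation share left about 0 and 4–5%.
- No systematic imbalance, as under randomisation: rejection was 4–5% with every adjustment. The standard deviation of the estimate was 12.8 or 15.5 per 1000 with the listed covariate, depending on its denominator, and about 8.6 with baseline coverage per registered adult.
- Participation 1.25 times higher in Arm 3: +19 per 1000 and 19% rejection if the covariate's denominator is participating providers' consultations, but +2 per 1000 and 5% if it is all PHCU consultations.

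**The case against.** The strongest reply is that the covariate is not the only protection. Control areas were chosen for comparability, including characteristics that affect healthcare. Country is in the models. Propensity score matching is planned on municipal and PHCU data, and an article may leave its details to an analysis plan. This stands in part. Registered numbers and staffing, the PHCU items listed, plausibly relate to consultation capacity, so matching may narrow a volume difference. But consultation volume is not among those items. Country cannot help, because Arms 2 and 3 both exist in every country and the difference at issue lies between areas within a country.

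A second reply concerns provider participation. Since "we estimate that approximately two-fifths of providers will consent to join the study", a reader might infer that the adjustment also misses differences in uptake. The documents do not support this as a general statement. The definition under Secondary outcomes allows a whole-PHCU denominator, under which low participation lowers the covariate and is largely captured. Participation is missed only if the denominator is participating providers' consultations.

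Third, a reader might infer that Hypotheses 2 and 3 are biased too. They are not: those arms are randomised within area, so any imbalance is by chance.

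Fourth, nothing in the protocol shows that consultation rates differ between the chosen areas. That is correct. The table shows how sensitive the estimate is, not how large the bias will be.

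**Conclusion.** The point holds for Hypothesis 1 and consultation volume. Outcome and covariate have different denominators, and no listed model term carries consultations per registered adult. In the non-randomised comparison an average difference in consultation rate between the areas therefore enters the estimate nearly in full: each 10% difference is worth 0.0075 at 12 months, a tenth of the planned effect, and 1.5 times that at 18 months. This assumes equal and constant measuring behaviour, the protocol's average rate of 0.10 consultations per registered adult per month, and a difference that area selection and matching have not removed.

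For Hypotheses 2 and 3 the cost is precision only. The stated power is unaffected. It would go too far to say that the trial has no other control of confounding, or that the Hypothesis 1 result will be biased by a known amount.

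**What to change.** 1. Add baseline-month adult consultations per registered adult as a PHCU-level covariate in the Hypothesis 1 model and, for precision, in the models for Hypotheses 2 and 3. Use the baseline month only, so that any later effect of municipal action on attendance is not adjusted away.
2. For the baseline measurement itself, either express it per 1000 registered adults or keep the listed proportion and state that its denominator is all adult consultations at the PHCU.
3. Name baseline consultations per registered adult among the propensity score matching variables.

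Adding the volume term is safer than relying on a rescaled measurement covariate alone. Baseline measuring may be close to zero: even at the planned Arm 1 level, one month gives 0.0325 / 12, about 2.7 per 1000, which says little about volume.

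Tally counts, consultations per provider and registered adults are already collected, so no new data are needed. The cost is about one degree of freedom among 30 PHCUs in Hypothesis 1 and 27 in each of Hypotheses 2 and 3.

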In the presence of municipal action, the short clinical package and short training do not lead to less measurement coverage than the standard clinical package and standard training.

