By Month 6, Hypothesis 3, that is, non-superiority of Arm 4 (standard package with municipal action and standard training) over Arm 3 (short package with municipal action and short training) will be tested. In the presence of clinical equivalence of a relative difference of the primary outcome, that is, the cumulative coverage of patients whose alcohol consumption is measured, of less than 10%, Arm 4 will be replaced by Arm 3 from month 8 onwards, figure 3.

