In the presence of municipal action, the short clinical package and short training do not lead to less coverage than the standard clinical package and standard training. In the presence of clinical equivalence of a relative difference of cumulative coverage of patients screened by less than 10% by month 6, the difference between Arm 3 (all 15 PHCU across the three countries) and Arm 4 (all 12 PHCU across the three countries) will be assessed with regression analyses. If Arm 4 is not superior to Arm 3, both arms will be collapsed into Arm 3 (shorter package) from month 8 onwards.

Dependent variable:

Cumulative results months 1 to 6 per 1000 patients.

Random effects:

Country as random intercept (test for inclusion).

Independent variables:

Condition:Length of clinical package (longer=Arm 4 vs shorter=Arm 3).Covariate:Proportion of consulting patients who have their alcohol consumption measured with a completed AUDIT-C instrument during the baseline measurement month.

It is postulated that Arm 4 is not significantly superior to Arm 3.

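### Hypothesis 3 claims that the short package loses no coverage, but a 10% screen without a confidence bound and a non-significant superiority test cannot show this with 15 against 12 PHCUs

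*Protocol article*

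**What the plan says.** The Introduction states Hypothesis 3 for the setting with municipal action: "the short clinical package and short training do not lead to less measurement coverage than the standard clinical package and standard training". The section on statistical tests repeats the claim and gives the rule. The regression of Arm 3 (15 PHCUs) against Arm 4 (12 PHCUs) on months 1–6 is introduced by the condition "In the presence of clinical equivalence of a relative difference of cumulative coverage of patients screened by less than 10% by month 6". The expected result is "It is postulated that Arm 4 is not significantly superior to Arm 3", and the consequence is "If Arm 4 is not superior to Arm 3, both arms will be collapsed into Arm 3 (shorter package) from month 8 onwards". The 10% limit carries no interval, significance level or power.

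Methods and analysis words the trigger differently. It announces a non-superiority test by month 6, then makes the 10% condition sufficient: "Arm 4 will be replaced by Arm 3 from month 8 onwards". The caption of Figure 3 assumes no superiority of Arm 4. The Discussion also calls this a test of non-superiority.

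Hypothesis 1 compares Arm 3 with Arm 2 on cumulative months 1–12 and 1–18. It does not say which PHCUs make up Arm 3 after a merge. The sample size section powers that comparison with 15 PHCUs per arm.

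**The concern.** The claim and the criterion do not match. To show that coverage is not lower, the data must exclude a loss larger than the margin. An observed difference under 10% excludes nothing unless its uncertainty is small. Failure to find Arm 4 superior is the expected result of an imprecise comparison, whatever the truth.

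One of the three stated hypotheses could therefore be declared supported by data compatible with a large loss of coverage. The same result also decides whether the arms are merged, which raises a secondary question about who belongs to Arm 3 in Hypothesis 1.

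**Working it through.** **Inputs.** 15 PHCUs (Arm 3) and 12 (Arm 4), from the Hypothesis 3 text. 15 000 adults per PHCU, "with an ICC for PHCUs of 0.03", and planned 12-month coverage of 0.0325, 0.075 and 0.15 in Arms 1, 2 and 3, from the sample size section. Month-6 coverage is not given. I take 0.15 (the planned 12-month value) and 0.075 (half of it, as if coverage accrued evenly) as an assumed range.

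**1. The plan's own power.** Design effect = 1 + (15 000 − 1) × 0.03 = 450.97, so each PHCU contributes 15 000/450.97 = 33.26 effective patients. With unpooled variance and two-sided 5%:
- Arm 2 vs Arm 1: SE = √[0.0325×0.9675/(12×33.26) + 0.075×0.925/(15×33.26)] = 0.01476; Φ(0.0425/0.01476 − 1.96) = 82.1% (stated 82%).
- Arm 3 vs Arm 2: SE = 0.01986; Φ(0.075/0.01986 − 1.96) = 96.5% (stated 96.5%).

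The model reproduces the plan, so it is fair to apply it to Hypothesis 3.

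**2. Precision for Hypothesis 3.** SE = √[p(1−p)/33.26 × (1/15 + 1/12)], without covariate gain.

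| | p = 0.15 | p = 0.075 |
|---|---|---|
| SE | 0.0240 | 0.0177 |
| Relative SE | 16.0% | 23.6% |
| 95% half-width (1.96 × SE) | 31% | 46% |
| Observed difference needed for significance (t, 25 df) | 33% | 49% |
| z for an observed 10% difference | 0.63 | 0.42 |

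For a 10% difference to be significant, the ICC would have to fall below about 0.0028 (p = 0.15) or 0.0013 (p = 0.075). Alternatively, covariates would have to remove about 1 − (10/32.9)² = 91% or 1 − (10/48.6)² = 96% of the between-PHCU variance.

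**3. How the screen behaves.** Chance that the observed difference is within ±10% of Arm 4 coverage (normal approximation):

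| True short-package deficit | p = 0.15 | p = 0.075 |
|---|---|---|
| 0% | 47% | 33% |
| 10% | 40% | 31% |
| 20% | 23% | 24% |
| 30% | 9% | 15% |

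Simulation with beta-distributed PHCU coverage gives about 21% at a 20% deficit with p = 0.075, hence 21–24%. If the screen looks only for an Arm 4 advantage of 10% or more, the pass rates are 73% and 66% at no deficit and 26% and 33% at a 20% deficit.

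**4. Power for an actual 10% margin.** With a true difference of zero and one-sided 0.025: Φ(0.626 − 1.96) = 9.1% at p = 0.15 and Φ(0.424 − 1.96) = 6.2% at p = 0.075. For 80% power, PHCUs per arm = 2p(1−p)(1.96 + 0.84)²/[(0.1p)² × 33.26], about 268 and 582.

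**5. Effect on Hypothesis 1, only if the 27 PHCUs are pooled.** The 12 former Arm 4 units carry seven months of the standard package. Their share of Arm 3 PHCU-months is 12/27 × 7/12 = 26% at 12 months and 12/27 × 7/18 = 17% at 18 months. If Arm 4 coverage were 20% higher in those months (assumption), the Arm 3 mean rises 0.26 × 20% = 5.2% and 0.17 × 20% = 3.5%. At 12 months that is 0.008 on 0.15, against a planned difference of 0.075.

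**The case against.** **The regression is not empty by construction.** It adjusts for baseline measurement and tests for a country intercept, while the screen mentions no adjustment. A crude gap under 10% could therefore hide an adjusted superiority. In simulation with the short package truly 20% worse, the adjusted test favoured Arm 4 in roughly 8% of screen-passing trials if baseline explained half the variance and 31% if it explained 70% (coverage 0.15). At coverage 0.075 the figures were 3.5% and 14%. Those R² values are assumptions. This stands: the regression adds little, but it cannot be said that it could never change the decision.

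**The screen gives some protection.** Without it, the superiority test would be non-significant 74–86% of the time at a true 20% deficit. Those figures do not describe the stated rule, which passes 21–24% of the time. This also stands, but a pass is still not evidence of non-inferiority, and equal packages fail the screen more often than they pass.

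**The trigger wordings are close.** Methods and analysis does announce a non-superiority test before giving the 10% condition, so the discrepancy is one of wording and will seldom change the outcome. It still needs reconciling.

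**Stronger readings.** A reader might infer that the merge contaminates Hypothesis 1. The documents do not establish this: Hypothesis 1 does not name the merged set, its power uses 15 per arm, and Figure 3 is not shown. A merge also requires an observed gap under 10%, so a shift nearer 0.26 × 10% = 2.6% is plausible if month 7 resembles the first six. A reader might also infer that a clearly better short package would fail the screen. That depends on reading the relative difference as unsigned, whereas the surrounding text asks about Arm 4 over Arm 3.

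**Conclusion.** The point holds for the inference in Hypothesis 3. As written, the rule can declare that the short package loses no coverage when the 95% interval spans about ±31% to ±46%. This rests on the protocol's ICC and cluster counts, on an assumed month-6 coverage of 0.075 to 0.15, and on little covariate gain. A much smaller ICC or very strong adjustment would narrow the interval.

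The conclusion does not depend on reading the 10% limit as a point estimate. If a two-sided equivalence test at 5% was meant, its power at this size is zero under the same model, so the screen would practically never be passed.

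The effect on Hypothesis 1 is a conditional risk of modest size and not an established error. It deserves a sentence because the dilution would differ between the 12- and 18-month totals, which is the contrast Hypothesis 1 tests.

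**What to change.** - Estimate the Arm 3/Arm 4 coverage ratio with its confidence interval from the planned regression. Claim Hypothesis 3 only if the lower bound, for example of a two-sided 95% interval, exceeds 0.90. Otherwise report Hypothesis 3 as inconclusive and give the interval.
- State that the month-8 merge is an operational decision and not evidence for Hypothesis 3.
- Reconcile the trigger in Methods and analysis with the one in the section on statistical tests.
- If the arms are merged, specify that Hypothesis 1 compares the 15 PHCUs originally allocated to Arm 3 with the 15 in Arm 2, as powered, with the pooled 27 as a sensitivity analysis.

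The cost is protocol or SAP wording, with no new data. The downside is that, at 6–9% power, Hypothesis 3 will very likely be reported as inconclusive.
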